### Study setting

The program is being implemented in two separate sites in the Republic of Ireland: West Dublin and Drogheda/Dundalk, Co. Louth^1^ (Northeast Ireland). Both are urban areas characterised by significant socioeconomic disadvantage and outcomes for children and young people in these areas compare unfavourably to national averages [31, 32]. The program will be delivered to groups of parents over two to three^2^ cycles per year. Each cycle comprises 2–3 parent groups comprising approximately 8–10 parents per group. Program delivery began in January 2015 in Site 1 (West Dublin) and roll-out in Site 2 (Drogheda/Dundalk) commenced in September 2015. The implementation of the PIN program is currently funded for a 2 year period (2014–2016) and five to six cycles of program delivery will be initiated during this period, although it is anticipated that program delivery will continue beyond this time point.

The delivery of the PIN program is funded jointly by the Irish government and a philanthropic organisation called the Atlantic Philanthropies, as part of a new Area-Based Childhood (ABC) program in Ireland [33]. The ABC program involves the implementation of 13 area-based approaches/initiatives to preventing and reducing child poverty in socially deprived areas of Ireland; two of these - the Blue Skies Initiative in Site 1 and the Genesis Program in Site 2 - are currently delivering the PIN program as one of a number of services in their area-based approaches. In each Site, the PIN program has been customised to meet community needs and local service delivery capacities. Thus, there are minor differences in the content and process of delivery between Site 1 and Site 2 (see Table 3) which will be explored through this process evaluation. The development and implementation of the PIN program is overseen in each site by a multi-disciplinary consortium of local stakeholders. These consortia employ a small number of staff whose role is to support participant recruitment and engagement, as well as service delivery. The program is delivered via usual care services and agencies, including statutory health care services (i.e. Public Health Nursing) and community-based organisations.

### Evaluation of the PIN program

A detailed process evaluation is being conducted in conjunction with a large-scale, longitudinal controlled before-and-after impact evaluation to assess the effectiveness of the program. Parents from within the sites where the program is delivered are recruited to the PIN program by Public Health Nurses and/or local, community-based service providers. Parents who are recruited to the program will subsequently be invited to participate in the research. A comparison group of parents who receive services as usual (and no PIN intervention) will be recruited from neighbouring areas with a similar profile to the intervention areas. Usual services in the non-intervention area for parent-infant dyads involve: one home visit from a PHN in the first 6 weeks after birth, regular developmental check-ups with a GP/PHN and vaccinations.

Prospective participants will be informed of the research verbally and by means of a brief brochure describing the research. Potential participants will then be asked to provide their written consent to be considered for inclusion in the research and for their details to be passed to the research team. If this consent is provided, names and telephone numbers are confidentially passed to the research team. Participants will then be contacted by the research team and furnished with a detailed information sheet. All participants must be aged 16 years or older and will provide written informed consent. A power calculation conducted on the basis of comparing the mean score of an intervention group on the Parenting Sense of Competence Scale (PSOC) [34] to that of a control group of the same size. Data will be required from 132 parents (66 in the intervention group; 66 in the control group) to allow over 80 % power to detect a difference in mean PSOC scores, between the intervention and control arm, of 3 units, based upon a SD of 6, this corresponds to a Cohen’s d of 0.5 (medium effect size). Therefore, a total sample size of 200 parents was recommended, assuming an attrition rate of 33 %.

Baseline assessments will be conducted with parents when the infant is approximately 6 to 14 weeks old. Subsequent follow-up assessments will be carried out when the infant is approximately 8, 16 and 24 months of age. The impact of the program, when compared to services as usual, will be investigated by assessing parent competencies and wellbeing, parent-infant relationships, child development and socioemotional adjustment. The process evaluation will be vital to interpreting the outcomes of the PIN program, while it also forms part of a wider goal to contribute to our understanding and knowledge of the effective implementation of complex early parenting intervention programs, including the relationships between program components, implementation processes, contextual factors and program outcomes. The process evaluation is being conducted by a multi-disciplinary research team independent of program development, implementation and delivery.

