### Intervention

The PIN program combines a range of developmentally-appropriate parent and infant supports which are delivered in a single intervention process from birth to 2 years of age (Fig. 2). The program is designed to be flexible in the sense that content and delivery can be tailored to parent/community needs, but it also has standardised core elements including two newly developed Incredible Years (IY) parenting programs [29]. Thus, parents who have recently given birth are offered a 16-week IY Parent and Baby (IY-PBP) program straddling the first 6 months of development. During this period, the IY program is delivered on alternate weeks in conjunction with information and awareness-raising and practical workshops and classes for new mothers (e.g. baby massage classes, weaning workshops, paediatric first aid, dental health and child safety). Tailor-made play workshops, as well as oral language development supports are also offered to parents when the infant is between the 9–12 months old. Subsequently, when the child reaches 18 months, the Incredible Years Parent and Toddler Program (IY-PTP) will be delivered [30]. Both Incredible Years programs are rooted in behavioral and social learning principles; they use DVD modelling, group discussions and role play to help parents acquire new skills aimed at promoting positive child adjustment and preventing maladjusted behavior.

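### The stated power of over 80% with 66 parents per arm assumes 132 independent parents and makes no allowance for group delivery in the intervention arm

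*Protocol article*

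**What the plan says.** The power statement is in the protocol article, section Evaluation of the PIN program. It compares the mean PSOC score of an intervention group with that of a control group of equal size. The number to be analysed is given as follows: "Data will be required from 132 parents (66 in the intervention group; 66 in the control group) to allow over". The power named there is more than 80%, for a 3-point gap between the arms and a standard deviation of 6. The target is then raised for losses: "Therefore, a total sample size of 200 parents was recommended, assuming an attrition rate of" 33%. No ICC, design effect or group size enters the calculation.

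The section Study setting describes delivery: "The program will be delivered to groups of parents over two to three" cycles a year, and "Each cycle comprises 2–3 parent groups comprising approximately 8–10 parents per group". The section Intervention says of the two Incredible Years programs, the standardised core, that "they use DVD modelling, group discussions and role play to help parents acquire new skills". Comparison parents come from neighbouring areas and receive usual services, which are a nurse home visit, check-ups and vaccinations. They are not treated in groups.

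**The concern.** Parents who learn together in a small discussion group share its facilitator, its dynamics and one another's influence. Their outcomes can therefore be more alike than those of parents in different groups. The authors themselves plan to examine variability in delivery across facilitators and parent groups (section Quantitative data). The power calculation nevertheless sets the between-group variance to zero.

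This makes a partially nested design, clustered in the intervention arm and not in the comparison arm. Any positive ICC raises the variance of the intervention mean and lowers the power. The margin is thin, because 64 per arm already gives 80.1%. What is at stake is how the PSOC result is read: a null result could be taken as coming from an adequately powered trial when the power was lower than stated.

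**Working it through.** **Inputs.** From Evaluation of the PIN program: 66 analysed per arm, difference 3, SD 6 (d = 3/6 = 0.5), attrition 33%, 200 recruited. From Study setting: about 8–10 parents per group. Assumed, because not stated: a two-sided 5% test, and ICC from 0.01 to 0.10.

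**Reproducing the plan's figure.** For independent parents, SE = 6·√(1/66 + 1/66) = 1.0445 and 3/SE = 2.872. Power is 81.4% by the noncentral t with 130 df (81.9% by the normal approximation). For attrition, 132/0.67 = 197, which accounts for the 200. No clustering allowance is hidden in either number.

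**Analysed group size.** 8 × 0.67 = 5.4 and 10 × 0.67 = 6.7, so about 6 analysed parents per group, or 66/6 = 11 groups. A smaller value is also possible. Study setting foresees five to six cycles of 2–3 groups, which is 10 to 18 groups. Parents are invited to the research only after recruitment to the program, so not every group member need be in the trial. 66 parents over 15–18 groups gives 4.4 to 3.7 per group, about 4.

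**Formulas.** With m analysed parents per group, the design effect in the intervention arm is DE = 1 + (m − 1)·ICC, and SE = 6·√(DE/66 + 1/66). Power is by the noncentral t with 130 df, and again with Satterthwaite df: (v1 + v2)² / [v1²/(k − 1) + v2²/65], where v1 = 36·DE/66, v2 = 36/66 and k = 66/m.

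Example, m = 6 and ICC 0.05: DE = 1 + 5 × 0.05 = 1.25. SE = 6·√(1.25/66 + 1/66) = 1.108. 3/SE = 2.708. Power is 76.7% with 130 df and 74.5% with 29.5 df.

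| Analysed per group | ICC | DE | Power, 130 df | Power, group-based df |
|---|---|---|---|---|
| 6 | 0.01 | 1.05 | 80.4% | 78.7% |
| 6 | 0.02 | 1.10 | 79.5% | 77.6% |
| 6 | 0.05 | 1.25 | 76.7% | 74.5% |
| 6 | 0.10 | 1.50 | 72.2% | 69.6% |
| 4 | 0.02 | 1.06 | 80.2% | 79.2% |
| 4 | 0.05 | 1.15 | 78.5% | 77.4% |
| 4 | 0.10 | 1.30 | 75.8% | 74.5% |

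**Break-even.** By the normal approximation, 80% power needs 1 + DE = 66 × (3/2.802)²/36 = 2.102, so DE = 1.102. With m = 6 this is ICC = 0.102/5 = 0.020. With the t distribution on 130 df it is about 0.014.

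**Conditional check on type I error.** If the analysis ignored groups, as the calculation does, the true two-sided error would be 2·[1 − Φ(1.96·√(2/(1 + DE)))]. With m = 6 this is 5.6% at ICC 0.02, 6.5% at 0.05 and 8.0% at 0.10.

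**The case against.** The strongest reply is that the calculation is correct for what it sets out to do. Its inputs give over 80% and its attrition step gives 200, so there is no slip of arithmetic. This stands: the fault is an independence assumption that the described delivery does not support.

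It is also fair that the ICC is unknown. At its low end the stated figure survives or misses by half a point (80.4% at 0.01 and 79.5% at 0.02 with 6 per group; 80.2% at 0.02 with 4). The group-based df put power below 80% with 6 per group even at ICC 0 (79.7%), but that depends on an analysis method the article does not fix. A one-sided 5% test would give 89.0% under independence and so more margin; the article does not state the sidedness.

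Three stronger readings are tempting, and the text does not support them:

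- A reader might infer that an unclustered test is planned and that type I error is therefore inflated. The article names no test or model for the PSOC comparison, and the section Quantitative data covers process data only. The type I figures are conditional, and the absent model is not itself a fault.
- A reader might use the full 8–10 parents per group and obtain larger losses. Nine analysed per group conflicts with the plan's own 33% attrition.
- A reader might suppose that the same parents and facilitator stay together through every component up to age two. The article does not say so.

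A SAP could specify a model with groups, but it could not make a power figure calculated without them correct.

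**Conclusion.** The concern holds in a limited form. The stated power is right only for 132 independent parents, whereas the intervention arm is treated in groups and no allowance is made. The loss from 81.4% is about 1 to 9 points with 6 analysed per group over ICC 0.01–0.10, or about 3 to 12 points with group-based df. With 4 per group it is about 1 to 6 points over ICC 0.02–0.10 before any df correction. These figures rest on an assumed ICC, a two-sided 5% test and analysed group sizes derived from the plan's numbers.

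It would go too far to say that the design cannot reach 80%. At an ICC of 0.01, or of 0.02 with small analysed groups, it about does, df aside. The supportable statement is that more than 80% power has not been shown and is lost once the ICC passes roughly 0.01–0.02 with 6 per group. This should be corrected, but it does not invalidate the trial.

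**What to change.** In Evaluation of the PIN program, restate the power for a partially nested design: clustering in the intervention arm only, analysed group size after attrition, and a short table over ICC 0.01–0.10 with the ICC labelled as an assumption. State the significance level and sidedness.

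Record each intervention parent's group. The article's description of the attendance checklists lists attendance per component and sessions per parent, but does not mention group. The PSOC comparison can then carry a random effect for parent group in the intervention arm only, with small-sample degrees of freedom.

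If PSOC is measured at the planned baseline assessment, adjust for it. The gain depends on an assumed baseline–follow-up correlation and is approximate. With a correlation of 0.5, 6 per group and ICC 0.10 to 0.05, power would be about 84–87% if adjustment shrinks both variance components. If only the within-group component shrinks, it would be about 81–86%, or 78–84% with group-based df.

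No additional parents are needed. The cost is revised wording, one recorded variable and one model term, together with a slightly less favourable stated power and somewhat wider intervals.

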### Study participants and data collection

Study participants will include program developers and implementers, as well as parents who take part in the PIN program. This process evaluation will be based on both qualitative and quantitative methods. Data collection will be conducted in two focused phases. During the first (initial) phase, data collection will focus on explicating the theory underlying the intervention, identifying the causal assumptions inherent in the program and outlining the activities, resources and factors which are assumed to be necessary to achieving program outcomes.

The second phase of data collection will expand on early findings and focus on exploring the processes involved in program implementation, patterns of engagement with the program, as well as the context in which the program is situated. Both quantitative and qualitative data will be gathered to explore program delivery processes, uptake and coverage, responses to the intervention, barriers to effective implementation of the program (e.g. program reach and participant engagement) and competing programs. As the PIN program is already being implemented, quantitative data relevant to program implementation (e.g. attendance sheets, participant feedback forms, facilitator feedback forms) will also be collected during phase one of data collection. An in-depth examination of program implementation and contextual factors will inform a critique of fidelity to the PIN program theory, while also highlighting adaptation/innovation and enabling the interpretation of findings from the impact evaluation. The data gathered throughout the process evaluation will be synthesised and analysed in order to identify the mechanisms through which the intervention activities produce intended or unintended effects.

#### Data sources

A wide range of data sources will be used to develop an in-depth understanding of the PIN program, the key activities, processes, inputs and outputs involved in, and conditions associated with, program delivery and implementation.

*Phase 1 data sources*Liaison with PIN program developers and implementers: The evaluation team and program developers and implementers are in regular communication. This will provide important insights into program logic, the choices made in relation to program content, preparation and groundwork for delivery as well as the planning and management of implementation.Documentation: A documentary analysis will be carried out which will involve the review and critical analysis of a wide range of relevant documentation including: meeting minutes; organisational reports and publications; online material; brochures; program proposals and descriptions; program manuals and written materials; official policy documents and demographic data; publications, reports, and journal articles. This data will contribute to refining ideas and identifying the conceptual foundations of the PIN program.Interviews: Program developers and implementers will be interviewed to explore the developmental origins of the PIN program, factors which influenced intervention design, development, and content, as well as related motivations, attitudes, perceptions and beliefs.

*Phase 2 data sources*Liaison with PIN implementers: Regular contact/meetings between the PIN program Project Coordinators (in both Site 1 and 2) and the evaluation team will be held to provide updates on: the development and implementation of program components; choices made in relation to program content and implementation; participant recruitment; the timing, delivery and implementation of intervention components; implementation and operational activities; as well as any planned and/or unplanned or forced changes to the program components and its delivery. Regular contact will also enable the evaluation team to monitor how operational and implementation activities evolve over time.Records and documentation: Records of recruitment procedures will be taken, including the number of prospective participants invited to participate in the program. Recruitment protocols, implementation manuals and other relevant documents (e.g. meeting minutes) will also be included in a documentary analysis. Demographic data, as well as routine documentation maintained by participating organisations (e.g. PHNs) including area birth rates, will be used to critique program reach.Impact evaluation data: Participant demographic data collected through the impact evaluation baseline assessments will be used to examine the characteristics of parents who engage with, and continue to participate in, the program. This data will be used to assess program reach and the maintenance of participant engagement. All parents who take part in the trial will also be asked, by means of a follow-up questionnaire administered by the evaluation team, to report uptake of services and supports which are external to the PIN intervention. In addition, parents in the control group will asked if they have accessed any of the treatment components (e.g. Baby Massage). This will enable the research team to examine if, and to what extent, contamination is occurring, thereby facilitating the accurate interpretation of program outcomes.Attendance checklists: Parent participants attendance for each program component will be routinely recorded by program facilitators. The number of sessions per component which individual parents attend, as well as the attendance of partners (if applicable), will also be recorded. Reasons for parental absence/non-attendance will be documented if available.Parent participant feedback forms: Parent feedback forms will be administered following the completion of each program component. These questionnaires will measure participant satisfaction as well as the perceived utility of the content of each program component, and facilitator effectiveness (Additional file 1).Implementer feedback forms: Program staff and facilitators will complete checklists/feedback forms after program sessions to record the extent to which essential material is covered, as well as the perceived response of participants. These forms will provide a measure of the extent to which the program is implemented as intended (fidelity); as well as highlighting any deviations from program content/protocols (Additional files 2, 3 and 4).Stakeholder survey: Key stakeholders involved in program development, implementation and delivery will be asked to complete a questionnaire to examine stakeholder attitudes and perceptions towards the PIN program, as well as individual capacity (e.g. skills, capacities, motivations and attitudes) and organisational capacity building processes (e.g. availability of training and/or other supports for program implementers) (Additional file 5). Findings from the questionnaire will help to build an understanding of the program delivery context.Interviews and group discussions: A series of one-to-one semi-structured interviews and group discussions will be conducted with a range of stakeholders as outlined below (Additional files 6 and 7). (a) Interviews will be conducted with program implementers (e.g. program support staff, facilitators) and management personnel from participating organisations; these will explore experiences of program implementation, barriers and challenges to implementation and the conditions within which the program is delivered (e.g. motivations, attitudes, perspectives, organisational infrastructures, policies, etc.). Group discussions will be conducted at a later stage and will focus on key stakeholders’ perceptions of how program implementation is progressing, any changes to program implementation, responses to environmental barriers and challenges and contextual changes (e.g. organisational changes).(b) Parent participants will be interviewed to explore issues pertaining to parenthood, including the experience of becoming a parent, parental expectations and the experiences and challenges/difficulties of parenting during infancy. These interviews will also focus on: parents’ experiences of taking part in the program; the extent to which they use the parenting skills, strategies, materials and information specified in the program; whether they continue to use such skills, strategies, material and information over time; barriers to program engagement/attendance; and factors which influence parenting experiences. A small number of partners of participating parents may also be invited to take part in qualitative interviews.

*Interview/group discussion procedure and participant sampling*. All interviews and group discussions will be audio-recorded with consent and guided using a schedule of open-ended questions. Interview/group discussion questions will be altered to reflect stakeholders’ experiences in relation the PIN and stages of program implementation (e.g. to explore emergent issues in implementation and/or participation in the PIN program). A purposive sampling method will be used to identify and recruit participants. Selection and recruitment will be designed to include as wide and diverse a range of perspectives as possible and to access participants’ expertise in relation to the key research questions. Key inclusion/selection criteria include the participants’ role within the development and/or delivery of the PIN program and their ability to provide insight into the key issues influencing, and affected by, program development and implementation. Parent participants will be selected from the overarching intervention group recruited to take part in the PIN program and the effectiveness evaluation (*n* = 100 approximately). Key demographic variables (e.g. socioeconomic disadvantage, marital status, age, parity, gender of child), program delivery cycle and level of program engagement (e.g. no. of sessions attended) will be used to recruit parents to the process evaluation. Care will be taken to ensure diversity and balance throughout the sampling process.

It is anticipated that approximately 40 key stakeholders will be invited to take part in interviews/group discussions. A responsive approach to sampling will be adopted; thus, as the research and data collection process progresses, potential participants will be identified and recruited on the basis of emergent findings. During the later stages of data collection, a small number of key informants will be re-interviewed or invited to take part in groups discussions in order to assess any potential changes over time in program implementation and delivery context, as well participants’ experiences, attitudes and beliefs.

